## Abstract

Primary Progressive Aphasia (PPA) is a syndrome due to different neurodegenerative disorders selectively disrupting language functions. PPA specialist care is underdeveloped. There are very few specialists (neurologists, psychiatrists, neuropsychologists, and speech therapists) and few hospital- or community-based services dedicated to the diagnosis and continuing care of people with PPA. Currently, healthcare systems struggle to provide adequate coverage of care that is too often fragmented, uncoordinated, and unresponsive to the needs of people with PPA and their families. Recently, attention has been gained by non-invasive brain stimulation techniques that allow a personalized treatment approach, such as transcranial Direct Current Stimulation (tDCS). The MAINSTREAM trial looks forward to introducing and evaluating therapeutic innovations such as tDCS coupled with language therapy in rehabilitation settings. A Multimodal Approach for Clinical Diagnosis and Treatment of Primary Progressive Aphasia, MAINSTREAM (ID: 3430931) was registered in the clinicaltrials.gov database (identifier: NCT05730023) on 15 February 2023.

## 1. Introduction

The Global Burden of Disease (GBD) study on disability revealed that 2.41 billion individuals worldwide had conditions that would benefit from rehabilitation and that this need was essentially unmet [1]. This is particularly true for neurological disorders, which are a leading cause of death (nearly 10 million deaths in 2019) and disability (349 million disability-adjusted life-years (DALYs) in the same period). Alzheimer’s and other dementias are one of the four leading contributors to neurological disability, and the number of DALYs continues to increase with an aging population [2]. The scarcity of established data on the determinants and outcomes of neurodegenerative conditions indicates that new knowledge is required to develop effective prevention and treatment strategies. Moreover, the demand for pharmacological and non-pharmacological treatments is increasing and has essential health service implications for managing these conditions. In this field, the Multimodal Approach for Clinical Diagnosis and Treatment of Primary Progressive Aphasia (MAINSTREAM) trial focuses on Primary Progressive Aphasia (PPA). PPA is a neurological syndrome due to different neurodegenerative disorders that selectively and progressively disrupt language functions [3], with a progressive impact on patients’ relationships, social networks, and participation in everyday activities based on communication [4]. PPA is characterized by various clinical symptoms of speech and language impairment due to the degeneration of language networks with heterogeneous degrees of severity [5]. The specificity of the clinical symptoms, reflecting the involved networks, enables the identification of different PPA phenotypes. The guidelines for the classification of PPAs have revealed three main variants: the non-fluent/agrammatic variant of PPA (nf/avPPA), the semantic variant of PPA (svPPA), and the logopenic/phonological variant of PPA (l/phvPPA) [6,7]. Moreover, the consensus criteria acknowledge that some patients do not fulfil the criteria for any PPA variants and are defined as “PPA unclassifiable” [7,8]. Each clinical subtype is characterized by the involvement of different linguistic areas and circuits: in nf/avPPA, degeneration involves the insular cortex, the posterior–inferior frontal gyrus (Broca’s region) and the superior temporal gyrus; in l/phvPPA, the progressive atrophy mostly affects the temporal–parietal junction; and in svPPA, atrophy is most profound in the anterior temporal lobes, including their mesial and inferior portions. Moreover, the PPA variants are probabilistically associated with different neuropathological substrates: frontotemporal lobar degeneration (FTLD) is associated with transactive response DNA-binding proteinopathy (TDP), FTLD-tau (nf/avPPA) or with Alzheimer’s disease (AD) pathology (l/phvPPA). As summarized, the knowledge about the neural substrates and mechanisms of PPA is limited. Currently, early diagnosis markers are unavailable, which might otherwise facilitate access to timely and effective therapies for persons living with PPA (plPPA).

### 1.1. Prior Research (Literature Review)

Interest in non-pharmacological therapies such as language training interventions, aimed at reducing the functional impact of communication difficulties on daily life and remediate language deficits in PPAs, has increased remarkably in the last decades [3,9]. An important issue is the application of a tailored approach based on language deficits and the patient’s needs [10] to be pursued in the early stages of the disease [11,12]. The literature reports different therapeutic approaches that have been utilized to create language treatments tailored to the individual PPA patient [13,14,15,16,17,18,19,20,21,22,23,24,25], inducing both immediate and long-term effects (e.g., [24,26]). However, most studies investigated the effectiveness of naming treatments in patients with a progressive word-finding difficulty [10,11].

We conducted a literature review and meta-analysis on the language treatments most commonly used in clinical practice among patients with different variants of PPA, focusing on enhancing spoken and written naming abilities [12,27]. Generally, the review indicated that language training could induce immediate post-treatment improvements in naming abilities in all variants of PPA. Moreover, despite the large variability in the results, the generalization and long-term effects of treatment gains may be noted after the training. Specifically, one well-investigated form of language intervention for plPPA is the lexical retrieval treatment [13]. Several treatment techniques target lexical retrieval [11,28]; for this reason, this approach is used flexibly in all variants of PPA. Phonological and orthographic treatment is most frequently dedicated to patients with a diagnosis of l/phvPPA, while semantic treatment is mainly applied to svPPA patients [12]. 

Some studies have highlighted the positive effects of telerehabilitation-based language treatment in PPA [22,29]. As many plPPA have limited access to traditional treatments, the use of telerehabilitation-based language treatment in PPA could help deliver care in a more widespread fashion [29]. Notably, Dial, et al. Dial, et al. [29] administered a treatment protocol aimed at promoting speech production and fluency in svPPA, l/phvPPA and nf/avPPA patients via either face-to-face or telerehabilitation appointments. Interestingly, no significant differences were found in terms of benefit, regardless of the modality of the intervention’s administration (face-to-face vs. telerehabilitation). This finding supports the application of telerehabilitation as an innovative instrument for delivering treatment to plPPA.

In recent years, there has also been a growing interest in the use of non-invasive stimulation techniques, such as transcranial Direct Current Stimulation (tDCS) and repetitive transcranial magnetic stimulation (rTMS) in PPA patients. Overall, treatment with rTMS or tDCS in plPPA yielded improved language abilities with respect to verbal fluency, written abilities, oral production, repetition, reading, comprehension, and naming after the stimulation [30]. Interestingly, some studies have suggested that using non-invasive brain stimulation techniques combined with language intervention increases the benefits of language training in plPPA [3,27,30,31]. Tippett, et al. Tippett, et al. [3] showed that language intervention improves language outcomes in plPPA, and tDCS can enhance the generalization and maintenance of positive language outcomes. A recent systematic review and meta-analysis from our group investigated the efficacy of language training on naming abilities in PPA, either alone or in combination with non-invasive brain stimulation [27]. It was shown that only language training combined with tDCS could improve the naming accuracy for untrained items, thus demonstrating a generalization effect. Moreover, the advantages of tDCS were evident at follow-up visits [27]. Finally, a randomized, double-blind, sham-controlled study applied tDCS associated with written naming/spelling therapy, revealing that tDCS can increase the effectiveness of language therapy in plPPA [32]. In addition, the study showed that tDCS efficacy differed across PPA variants, with greater effects of the combined treatment (tDCS plus spelling therapy) on written naming abilities in nf/avPPA and l/phvPPA. In contrast, in the svPPA patients, tDCS did not significantly improve the effectiveness of language therapy for trained and untrained items [32]. These studies suggest that the use of these non-invasive techniques coupled with language intervention is more effective than language training or non-invasive brain stimulation applied alone [27,30]. 

Despite the aforementioned benefits of treatment, the neural and biological correlates of cognitive improvements induced by rehabilitation techniques in PPA and the variables that might be related to successful recovery remain poorly understood [33]. Moreover, the prediction of individual patient responses to combined behavioral and neuromodulation treatment remains an elusive goal. 

### 1.2. Objectives

In this double-blind, randomized, controlled pilot study, we aim to test tDCS neuromodulation coupled with language therapy in rehabilitation settings. In particular, we will evaluate the short-term and long-term effects of active tDCS over the dorsolateral prefrontal cortex (DLPFC) combined with individualized language training vs. placebo DLPFC-tDCS with individualized language training in a large sample of patients with mild PPA. In particular, we aim to establish if the combined use of active tDCS and individualized language training in mild PPA patients can improve cognitive and functional performance. Moreover, we aim to evaluate the changes in brain activity and molecular markers as they relate to the intervention. To date, little is known about the mechanisms of the treatment’s effects. This trial could partially fulfil the need for new rehabilitation instruments to be used in daily disease management. It will increase understanding of the neural and biological characteristics linked to the effect of language treatment and non-invasive brain stimulation application in PPA.

## 2. Materials and Methods

The protocol of the present study has been prepared as outlined in the “Standard Protocol Items: Recommendations for Interventional Trials” (SPIRIT) guidelines (Figure 1).

The study will be conducted in accordance with the Declaration of Helsinki. It has been approved by the Ethics Committees of the Istituto di Ricovero e Cura a Carattere Scientifico (IRCCS) Centro San Giovanni di Dio, Fatebenefratelli, Brescia, Italy (protocol number: 52-2022), of the IRCCS Fondazione Mondino, Pavia, of the Fondazione IRCCS Ca’ Granda, Ospedale Maggiore Policlinico, Milan and of IRCCS Fondazione Don Carlo Gnocchi, Milan.

### 2.1. Trial Design and Setting

This multicentric study is a double-blinded, randomized, controlled pilot study involving 60 patients with mild PPA, defined using the Progressive Aphasia Severity Scale (PASS) [34,35], recruited from IRCCS Istituto Centro San Giovanni di Dio, Fatebenefratelli, Brescia; IRCCS Fondazione Mondino, Pavia; Fondazione IRCCS Ca’ Granda Ospedale Maggiore Policlinico, Milan, and Fondazione Don Carlo Gnocchi—ONLUS, Milan, Italy.

After recruitment, the subjects will be randomized into one of two parallel groups: (i) active tDCS over the DLPFC combined with an individualized language training group or (ii) placebo DLPFC-tDCS with an individualized language training group. The two groups will be matched for age, education, and language deficit severity. All participants will undergo a clinical, cognitive, and language evaluation at the baseline (T0), post-treatment (T1), and at the 3-month (T2) follow-up. Magnetic Resonance Imaging (MRI) and biomolecular data will be collected at T0 and T1 (after the treatment). The trial work plan is shown in Figure 2.

### 2.2. Sample Size

The sample size calculation was computed using G*Power 3 software [36,37]. The sample size for this pilot study was determined based on previous work [38] and was computed for the primary outcome variable (an increase in naming accuracy). An eta square of 0.25 of the interaction between time and the experimental group was considered for the effect size calculation. A minimum sample size of 12 subjects is required for a 90% powered study (alpha = 0.05). The resulting number was increased to 30 subjects per group based on the 20% expected dropout rate among the subjects and because of the considerable individual variability expected from the inclusion of all PPA variants.

### 2.3. Study Population, Recruitment, and Randomization

According to the sample size calculation, the MAINSTREAM trial has a target enrollment of 60 patients diagnosed with mild PPA, defined using the Progressive Aphasia Severity Scale (PASS) [34,35]. Eligible patients who meet all inclusion criteria (see the paragraph below) will be randomized using an adaptive randomization procedure. Clinicians and patients will be blinded to the trial intervention. The group allocation will be masked to the statistician conducting the data analysis.

### 2.4. Inclusion and Exclusion Criteria

Formal criteria-based diagnosis of PPA will be applied, and the variant will be determined according to consensus criteria [7].

The inclusion criteria for participants will be:
Age eligible for the study: 40 years or older (Adult, Older Adult); Agreement to participate by signing the informed consent form; Diagnosis of PPA according to the current clinical criteria [7]; Mild PPA defined using the Progressive Aphasia Severity Scale (PASS) [34,35];Native Italian speakers.

The exclusion criteria will be:Presence of developmental disorders;Presence of any medical or psychiatric illness that could interfere with completing assessments;Presence of any medical condition representing a contraindication to tDCS.

### 2.5. Trial Interventions

All patients will undergo treatment sessions of 45 min each on five consecutive days a week for two weeks: -30 patients will receive active tDCS over DLPFC (anode over the left DLPFC with the cathode over the right supraorbital region) while performing individualized language training;-30 patients will receive placebo tDCS over DLPFC during individualized language training.

#### 2.5.1. tDCS

All patients will receive two weeks of tDCS stimulation (Active or Placebo) during the individualized language training. Active tDCS (anode over the left DLPFC with the cathode over the right supraorbital region) will be delivered by a battery-driven stimulator (HDCStim System, Newronika) through a pair of saline-soaked sponge electrodes (35 cm^2^ each). The active electrode will be applied over the left DLPFC, and the reference electrode will be fixed over the right supraorbital region. We will develop a model based on the patient’s MRI average data to find the optimal electrode montage since cortical thinning and ventricular enlargement could substantially affect the current pathway. A constant current of 2 mA will be applied for 25 min (current density of active electrode 0.06 mA/cm^2^) with a ramping period of 10 s at the beginning and end of the stimulation, starting five minutes before the beginning of the language training. The current density will be maintained below the safety limits [39,40]. For placebo stimulation, the setting will be the same, but the current will be turned off shortly after initiation.

#### 2.5.2. Language Training

The language treatment will be based on the combination of compensation approaches and individualized language training, including an impairment-directed treatment approach for naming. An individual trained and untrained pictures list will be selected as detailed in the “*Primary outcome measures*” paragraph below. The subjects will receive individualized language training treatments that include several steps designed to encourage the strategic recruitment of spared semantic, orthographic, and phonological knowledge as well as episodic/autobiographical information to facilitate word retrieval and to elicit the production of the target object [26,32,41]. In this regard, the individualized language training will incorporate elements of the most frequently used treatments in clinical practice among patients with different variants of PPA, such as lexical retrieval treatment [11]; phonological and/or orthographic treatment [42,43,44]; and semantic treatment [17,45]. At each step, in the case of difficulties or errors, the patient will be helped by the therapist to provide the correct response. The patient will be seated in front of a computer screen in a quiet room while the therapy protocol will be displayed using Microsoft PowerPoint. The pictures will show the items to be trained, and the treatment will involve several steps:

*Step 1: Semantic Feature Analysis*. The patient will be asked questions that are semantically related to the image presented in the center of the computer screen *(e.g., Is this a?; Where do you find it?; What does it look like?/What is it made of?/What color is it?; It reminds me of?; What is it for?/What is it used for?/Which verb can be associated?*). In the case of difficulty in answering any question, the therapist will make suggestions.

*Step 2: Script Training*. The patient will be asked to formulate a sentence using the verb evoked during the previous step (Semantic Feature Analysis). Subsequently, the patient will be asked to read aloud the sentence presented on the screen; in the case of reading difficulties, the sentence will be produced by the therapist, and the subject will be asked to repeat it. 

*Step 3: Phonemic cue*. The participant will be asked to orally produce the initial sound of the word corresponding to the image presented in the center of the screen. In the case of an error, the initial letter will be shown, and the patient will be asked to produce the sound. For the next cue, the correct sound will be pronounced by the therapist, and the participant will be asked to repeat it. 

*Step 4: Oral reading*. The target written word will be presented on the computer screen, and the participant will read it aloud; in the case of reading difficulties, the word will be produced by the therapist, and the subject will be asked to repeat it.

*Step 5: Articulatory suppression task*. This involves interference with articulatory codes caused by the uttering of an irrelevant speech sound (i.e., bla, bla, bla). In the suppression condition, participants will receive instructions to start uttering the syllable “bla”. 

*Step 6: Oral picture naming*. The target picture will be presented on the computer screen, and the participant will be asked to retrieve its correct name.

*Step 7: Oral repetition*. The target word will be spoken by the therapist, and the participant will be asked to repeat it three times. 

*Step 8: Articulatory suppression task*. This involves interference with articulatory codes caused by the uttering of an irrelevant speech sound (i.e., bla, bla, bla).

*Step 9: Oral picture naming*. The target picture will be presented on the computer screen, and the participant will be asked to retrieve its correct name.

At the end of this treatment, the therapist will have 20 additional minutes to focus on other treatment strategies based on the individual patient’s language difficulties. 

The rehabilitation program will include a therapist guide and a patient workbook. The therapist guide will walk the therapist through the program and will explain what to say and do with the patient in each session.

### 2.6. Outcome Measures

#### 2.6.1. Primary Outcome Measures

The primary outcome measure will be the change from baseline (T0) to post-treatment (T1) and follow-up assessment (T2) in object- and action-naming task scores, as assessed by the International Picture Naming Project (IPNP) Task [46]. 

At the baseline assessment (T0), the patients will undergo two sessions of oral object naming to select object stimuli for the treatment (trained items) and control object stimuli for the assessment of generalization effects (untrained items). Pictures for the oral naming task will include 300 black-and-white drawings of objects taken from the UCSD Center for Research in Language—International Picture-Naming Project corpus [46]. This database provides norms and lexical information (frequency, age of acquisition, etc.) for picture naming in seven languages. The pictures have been tested and normed on healthy and patient populations [46]. In this protocol, the pictures for the oral naming task will be displayed twice (on two consecutive days) on a computer screen using Microsoft PowerPoint; each picture will be presented for a maximum of 6 s. Each participant will be asked to name the object, and oral responses will be recorded.

The pictures not correctly named by the participant in at least one out of the two oral naming sessions will be further split into two sets: the “therapy” list, which will include the items to be trained (trained stimuli), and the control stimuli list, which will include items not to be trained (untrained stimuli). The two lists will be balanced as closely as possible for several variables (e.g., word frequency, number of syllables, semantic category, etc.). The procedure that will be applied to select the “therapy” and “control” lists will produce a personalized set of items for each participant, which ensures the within- and across-subject validity of the design. The accuracy in naming trained and untrained items will be assessed at the end of the rehabilitation (T1) and during follow-up visits (T2). 

Moreover, naming oral action items will be evaluated to assess generalization effects. 

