### 2.8. Statistical Analysis

A repeated-measures analysis will be used to compare pre-treatment (T0) versus post-treatment (T1) and follow-up (T2) variables for the two groups. Regarding MRI, the data will be analyzed using repeated-measures ANOVAs by testing different experimental factors: timing (T0, T1), hemisphere, and electrode site. Correlations between cognitive/functional changes, imaging biomarkers, and molecular biomarkers will be assessed by using Pearson’s correlation coefficient.

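### If T0 list scores come from the sessions that selected the failed items, both naming lists are expected to rise with no treatment effect; the between-arm contrast is safe, within-arm change is not

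*Protocol article*

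**What the plan says.** Protocol article, section 2.6.1, sets out the following.

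- **Purpose of the T0 sessions:** "At the baseline assessment (T0), the patients will undergo two sessions of oral object naming to select object stimuli for the treatment" and, from the same sessions, for the untrained control list.
- **Selection rule:** "pictures not correctly named by the participant in at least one out of the two oral naming sessions will be further split" in two, one list to be trained and one not.
- **Pool:** 300 object drawings, each shown on two consecutive days.
- **Outcome:** "The primary outcome measure will be the change from baseline (T0) to post-treatment (T1) and follow-up assessment (T2) in object- and action-naming task scores".
- **Later testing:** accuracy on both lists is measured at T1 and T2. The section does not say how the T0 value of a list is scored, or whether the primary object score is list accuracy or the whole picture set.
- **Claim made for the procedure:** it yields personal item sets, "which ensures the within- and across-subject validity of the design".

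Section 2.8 adds: "A repeated-measures analysis will be used to compare pre-treatment (T0) versus post-treatment (T1) and follow-up (T2) variables for the two groups". It also plans Pearson correlations between cognitive or functional changes and the imaging and molecular biomarkers. Section 2.2 sizes the trial on the interaction of time and group.

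**The concern.** The same two sessions appear to do two jobs: they pick the items and they supply the baseline. An item enters a list because it was failed, and some of those failures are chance misses on words the patient can often name. The T0 score on the chosen items therefore lies below the patient's true accuracy on them, and the next test is expected to be higher even if nothing has changed.

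Three uses of the data are exposed:

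1. The untrained list is there to show generalisation. A T0-to-T1 rise on that list within an arm could be taken for generalisation when it is only selection.
2. The time main effect in the repeated-measures analysis mixes training benefit with this artefact.
3. The artefact varies with baseline accuracy. If naming change is among the changes correlated with biomarkers, a marker related to severity could correlate with change for this reason alone. Randomisation does not protect a correlation.

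**Working it through.** **The plan's own figures.** The article states no expected change without treatment and no T0 accuracy, so there is no figure of its own to reproduce on this point. The nearest figure, 12 subjects in section 2.2, has no bearing here. It does reproduce as a total: f² = 0.25/0.75 = 0.333; with two time points and correlation 0.5, λ = 0.333 × 12 × 2/0.5 = 16, and power is 0.949.

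**Inputs.** From section 2.6.1: two T0 sessions, 300 pictures, selection on at least one failure. Assumed, because the documents do not give them: mean naming accuracy μ, and the spread of item difficulty, modelled as a Beta distribution with between-item correlation icc (precision s = 1/icc − 1). Constant true ability and no treatment effect are also assumed.

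**One item with true naming probability p.**

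- Chance of selection: 1 − p².
- Expected T0 accuracy given selection: p(1 − p)/(1 − p²) = p/(1 + p). It is the same for either session alone or for their average.
- Expected T1 accuracy: p.
- Artefact: p − p/(1 + p) = p²/(1 + p). For p = 0.5 this is 16.7 points; for p = 0.7, 28.8 points.

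A selected item has at most one correct answer in two, so a list's T0 score averaged over both sessions cannot exceed 50%. T1 has no such ceiling.

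**Items of varying difficulty.** Artefact = E[p²(1 − p)]/E[1 − p²]. It is positive unless every item is always named or never named.

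Worked case, μ = 0.7 and icc = 0.4 (s = 1.5, first Beta parameter 1.05):

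- E[p] = 0.700; E[p²] = 0.700 × 2.05/2.5 = 0.574; E[p³] = 0.574 × 3.05/3.5 = 0.500.
- T0 = (0.700 − 0.574)/0.426 = 29.6%.
- T1 = (0.700 − 0.500)/0.426 = 46.9%.
- Rise with no effect: 17.3 points.

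Rise in percentage points, at-least-one-failure rule:

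| μ | icc 0.2 | icc 0.4 | icc 0.6 | icc 0.8 | icc 0.9 |
|---|---|---|---|---|---|
| 0.5 | 14.3 | 11.5 | 8.3 | 4.5 | 2.4 |
| 0.6 | 18.4 | 14.4 | 10.2 | 5.5 | 2.9 |
| 0.7 | 22.7 | 17.3 | 12.0 | 6.4 | 3.3 |
| 0.8 | 27.3 | 20.4 | 13.9 | 7.4 | 3.8 |

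Between-session agreement is 1 − 2μ(1 − μ)(1 − icc). At μ = 0.7 it is 0.66, 0.75, 0.83 and 0.92 for icc 0.2, 0.4, 0.6 and 0.8. The first three icc columns give 8 to 27 points; the last two show how the rise shrinks when answers are very consistent. A wider grid (μ 0.3 to 0.9, icc 0.2 to 0.9) gives about 1 to 32 points.

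**The other reading of the rule.** If an item must be failed in both sessions, T0 is 0% by construction and the artefact is E[p(1 − p)²]/E[(1 − p)²]: about 12 to 53 points for μ 0.5 to 0.8 and icc 0.2 to 0.6. The worked case gives (0.700 − 1.148 + 0.500)/(1 − 1.4 + 0.574) = 0.052/0.174 = 30 points.

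**Between-arm contrast.** In a null simulation (30 per arm, 300 items, mean accuracy about 0.7, icc 0.4, 1,000 runs) the within-arm gain was 17.3 points and the active-minus-placebo difference −0.1 point. The rejection rate was 6.2%, with a Monte Carlo error of about 0.7 points.

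**Dependence on baseline.** At icc 0.4 the artefact goes from 11.5 points at μ = 0.5 to 20.4 at μ = 0.8. In simulation its correlation with baseline accuracy was about 0.3 to 0.5.

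**Gain from adjusting.** In four simulated scenarios, replacing the change score by T1 accuracy adjusted for total T0 accuracy lowered residual variance from 0.00874 to 0.00808, 0.01401 to 0.01339, 0.00616 to 0.00555 and 0.01078 to 0.00934, that is, by about 4% to 13%.

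**The case against.** The strongest reply is that the trial's question is comparative. Section 1.2 sets active against placebo tDCS, both with training; section 2.2 sizes the trial on time by group; section 2.8 compares time points for the two groups. Both randomised arms use the same item rule, so the artefact cancels in expectation. The Discussion's generalisation argument is also comparative: it credits generalisation only to training combined with tDCS, so a similar rise in both arms would not support it. All of this stands. A reader might infer that the primary active-versus-placebo result is biased; neither the documents nor the simulation supports that.

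Second, the scoring is inferred. Section 2.6.1 never says that T0 list scores come from the selecting sessions. A score over all 300 pictures, or action naming if it is not failure-selected, would be free of the artefact. This stands too, and is why the point is conditional. The section describes no other T0 object-naming session, however, so the condition is the natural reading.

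Third, a reader might infer that the lists are not balanced on T0 score, or that the trained list is not chosen at random. The article is only silent: its balancing variables are examples in an open list, and such detail may sit in the full protocol. Neither is an error shown here.

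The reply does not rescue the claim that the procedure ensures within-subject validity, or the planned change correlations.

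**Conclusion.** The point holds in conditional form. If the T0 list scores are those of the selecting sessions, both lists are expected to rise without any treatment effect, whichever way the failure rule is read. The direction needs only that some items are sometimes named and sometimes missed.

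The size does rest on assumptions: about 8 to 27 points for mean accuracy 0.5 to 0.8 and icc 0.2 to 0.6, a few points at high consistency, more under a failed-twice rule. A reader might want one firm figure, such as 12 to 26 points; that is merely what mean accuracy 0.6 to 0.9 with Beta precision 1 to 2 gives, and the documents support no such choice. Disease progression by T2 could also offset part of the rise.

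The time main effect, within-arm gains (above all on untrained items) and correlations using raw naming change are affected. The randomised contrast is not. The wording on validity claims too much for pre-post change. This should be corrected, but it does not threaten the main comparison.

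**What to change.** - State whether the primary object-naming score is list accuracy or accuracy over all 300 pictures, and how T0 is scored.
- Define the effect on each list as the between-arm difference in T1 and T2 accuracy, adjusted for total T0 accuracy over all 300 pictures in both sessions. These data are already collected.
- Label within-arm T0-to-T1 change on the selected items as descriptive only.
- Do not enter raw change on those items in the biomarker correlations without adjusting for T0 accuracy.
- If not already done, add T0 score (0 of 2 or 1 of 2) to the list-balancing variables and draw at random which list is trained.
- Qualify the sentence on within- and across-subject validity.

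The cost is wording, one balancing variable and one random draw per patient, with no new testing. If an unbiased within-arm change is wanted, a separate naming session on the chosen lists before treatment would bring the expected artefact to zero, at the price of that session. An item-level logistic mixed model, which would also weight unequal list lengths, is optional.
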